# A randomized, double-blind, placebo-controlled phase III study evaluating the preventive effect of diclofenac cream on capecitabine-related hand-foot syndrome: study protocol of J-SUPPORT2401/JORTC-SUP06 (J-DIRECT)

**DOI:** 10.1007/s10147-025-02789-z

**Published:** 2025-05-14

**Keywords:** Capecitabine-induced hand-foot syndrome, Topical diclofenac cream, Protocol

## Abstract

**Background:**

Clinical evidence on preventive therapy for capecitabine-induced hand-foot syndrome (HFS) is limited, and moisturizing and avoiding local pressure are recommended in guidelines. Although the precise pathogenesis and mechanisms of HFS remain unclear, inflammatory reactions are thought to be involved. The preventive effects of topical diclofenac gel have been reported from India. However, the trial did not evaluate its preventive effect for the sole, and the HFS incidence in the control group was lower than that in previous reports. Therefore, this study aims to confirm the preventive effects of diclofenac sodium 0.1% cream for capecitabine-induced HFS.

**Methods:**

This is a multicenter, randomized, double-blind, placebo-controlled, phase 3 trial. Patients scheduled to receive capecitabine-containing chemotherapy are enrolled, and participants are prophylactically treated with topical diclofenac sodium 0.1% cream or placebo alongside standard preventive therapy. The primary endpoint is an incidence of grade 2 HFS within 3 months. The secondary endpoints include time to onset of HFS, incidences of dose reduction, schedule delay, discontinuation caused by capecitabine-induced HFS, dose intensity of capecitabine, an incidence of grade ≥ 2 peripheral sensory neuropathy, incidences of other capecitabine-related adverse events (nausea, vomiting, appetite loss, diarrhea, oral mucositis, pigmentation, abnormality of liver and renal functions, and neutropenia).

**Discussion:**

If this study meets the primary endpoint, a new standard preventive therapy for HFS will be established. Moreover, the use of topical diclofenac cream alongside high-dose capecitabine may enhance chemotherapy efficacy.

## Introduction

Hand-foot syndrome (HFS) is the most common adverse event induced by capecitabine, often deteriorating patient’s quality of life (QOL) [1]. In randomized-controlled trials (RCTs) of systemic chemotherapy for colorectal cancer, the incidence of any grade HFS caused by capecitabine have been reported to be approximately 30% to 80% [2–10], whereas real-world data suggest that it is over 90% [11]. Severe HFS causes symptoms, such as swelling, blisters, desquamation, and ulcers, often leading to treatment interruptions, delays in the treatment schedule, dose reduction, and discontinuation of capecitabine. One study showed that 17–24% of patients with metastatic colorectal cancer receiving capecitabine monotherapy required dose and schedule modifications due to HFS [12]. Additionally, while it has been reported that dose intensity of capecitabine influences the outcomes of adjuvant chemotherapy for colon cancer [13], moderate or severe HFS requires treatment modifications (interruption and/or dose reduction) [14]. Therefore, managing HFS is crucial not only for maintaining patient’s QOL but also for ensuring the therapeutic efficacy of capecitabine [15]. However, a standard preventive therapy has not been established due to inconsistent results regarding the effectiveness of topical urea [16, 17], exfoliating agents [18], celecoxib [19, 20], vitamin E [21], and pyridoxine [22] for HFS. Currently, moisturizing and avoiding local pressure [23–25] are recommended as standard management methods for preventing capecitabine-induced HFS [26].

The mechanism of HFS involves the inhibition of the skin basal cell proliferation, drug secretion from the eccrine sweat glands, the involvement of drug degradation products [15, 27], and an inflammatory response triggered by interleukin (IL)-1a, IL-1b, IL-6, and reactive oxygen species [28]. Based on this rationale, a large phase III study demonstrated that celecoxib has a preventive effect on HFS. However, its clinical use has been limited because of concerns about adverse events caused by the long-term use of non-steroidal anti-inflammatory drugs (NSAIDs). Moreover, clinical trials have evaluated the preventive effects of medium-class topical steroids [29] and topical diclofenac [30]. Corticosteroids exert their anti-inflammatory effects by inhibiting the release of chemical mediators. Oral dexamethasone (8 mg/day, followed by tapering) was administered to patients with pegylated liposomal doxorubicin-induced HFS in a prospective study [31], which reported that patients receiving dexamethasone required fewer treatment modifications, such as schedule delays or dose reductions than those not receiving dexamethasone. Other case reports have suggested that corticosteroids may be effective against cytarabine- and vinorelbine-induced HFS [32, 33]. NSAIDs inhibit the production of cyclooxygenase (COX)-2, which is believed to contribute to the development of HFS [34]. Thus, anti-inflammatory agents may help prevent HFS caused by cytotoxic anti-tumor agents. Although the effectiveness of oral COX-2 inhibitors has been reported [19, 20], safety concerns remain.

Since topical formulations offer better safety by reducing the systemic effects of NSAIDs, the topical use of anti-inflammatory agents, such as corticosteroids and NSAIDs, is expected to prevent HFS without major safety concerns. Recently, the preventive efficacy of topical diclofenac was reported in India (D-TORCH study) [35], demonstrating that the prophylactic administration of topical diclofenac reduced the frequency of grade ≥ 2 HFS by 11.2% (3.8% vs 15.0%). However, the incidence of HFS in the placebo group of the D-TORCH study was substantially lower than that in other Asian studies (Table 1). Additionally, the D-TORCH study evaluated the effectiveness of topical diclofenac only on the hands, not the soles. Furthermore, while the study used a diclofenac gel base, the isopropanol in the gel may cause skin dryness and irritation, potentially worsening HFS symptoms. A cream-based formulation is generally considered more suitable than a gel for preventing HFS.

**Table 1 Tab1:** Difference of the incidence of HFS induced by capecitabine in India (D-TORCH study) and other Asian countries in randomized-controlled trials

					Incidence rate of HFS (any grade)		Incidence rate of HFS (grade 2 or 3)		Incidence rate of HFS (≥ grade 3)	
			Number of patients		%		%		%	
Country	Intervention	Blind	Intervention	Control	Intervention	Control	Intervention	Control	Intervention	Control
China 2010 [19]	Celecoxib	No	51	50	29	52	11.76	30	1.96	10
China 2012 [20]	Celecoxib	No	68	71	57.4	74.6	14.7	29.6	2.9	8.5
South Korea 2010 [44]	Pyridoxine	Yes	180	180	64	76.1	12	15.4	3.3	5
Japan 2014 [45]	Pyridoxine	No	30	30	NA	NA	60	60	NA	NA
Singapore 2017 [46]	Pyridoxine	Yes	105	105	61	66	32	37	4	2
Japan 2018 [47]	Pyridoxine	No	66	67	77	69	34	34	4	4
Japan 2020 [48]	Eppikajutsuto (Kampo medicine)	No	10	12	70	83.3	40	50	20	8.3
China 2021 [18]	Lithium containing topical and moisturizing cream	Yes	51	54	56.8	75.9	4.8	16.7	6.0	16.7
India 2020 [36]	Structured teaching module	Yes	135	134	64.4	62.5	33.3	32.8	5.2	6.8
India 2024 [35]	Topical diclofenac	Yes	130	133	6.1	18.1	3.8	15	2.3	5.3

This multicenter, randomized, double-blind, placebo-controlled, phase 3 trial aims to confirm the preventive effect of diclofenac sodium 0.1% cream for capecitabine-induced HFS.

## Methods

### Study design

This is a multicenter, randomized, double-blind, placebo-controlled, phase 3 study. The study protocol was reviewed and approved by the certified Clinical Research Review Board of the University of Tokyo (approval number 2024505SP). The study is being conducted in compliance with the Clinical Trials Act in Japan and registered in the Japan Registry of Clinical Trials (jRCT) as jRCTs031240705.

### Participants

The following patients are included in this study: (i) patients with colorectal, breast, or gastric cancer planned to receive chemotherapy containing capecitabine (≥ 800 mg/m^2^ b.i.d); (ii) Eastern Cooperative Oncology Group performance status of 0–1, (iii) aged ≥ 18 years; and (iv) providing written informed consent. Exclusion criteria are as follows: (i) history of aspirin-induced asthma; (ii) presence of other skin diseases, skin lesions due to chemotherapy on the palms or soles, or dermatitis that makes it difficult to evaluate the efficacy of the study drug; (iii) history of hypersensitivity to local diclofenac; (iv) conditions requiring the constant use of steroids or NSAIDs; (v) scheduled to receive other anti-tumor agents (e.g., multi-kinase inhibitors for anti-angiogenesis) that may interfere with the evaluation of efficacy of the study drug; (vii) pregnancy, breast feeding, or inability to adhere to contraception during the study period; and (viii) sensory palsy in the palms or soles.

### Randomization

After confirming eligibility, patients are registered using an independent central registration system. They are randomized in a 1:1 ratio to receive either diclofenac sodium 0.1% cream or a placebo cream using the minimization method, adjusted for sex (male vs. female), planned dose of capecitabine (≥ 800 mg/m^2^, < 1000 mg/m^2^, ≥ 1000, < 1250 mg/m^2^, ≥ 1250 mg/m^2^), and participating institution.

### Chemotherapy

Combination with other anti-tumor agents (e.g. oxaliplatin) and radiation (except for the palms and soles) is allowed if it includes capecitabine (≥ 800 mg/m^2^). However, multi-kinase inhibitors (e.g., lapatinib) will not be allowed. Dose interruptions, delays, reductions, and discontinuations are allowed at each physician’s discretion.

### Intervention

Both diclofenac sodium 0.1% cream and placebo are white cream products. The hydrophilic cream, which is the base material of diclofenac sodium 0.1% cream, is selected as the placebo. Since there is no noticeable difference in appearance or odor, double-blindness is ensured. Topical diclofenac sodium 0.1% cream or placebo is applied to the palms and soles twice daily in the morning and evening. More than one fingertip unit (one fingertip unit provides 0.5 g) of the study drug is applied to each palm and sole. This preventive treatment is initiated in the evening on day 1 and continued throughout the study period. All patients receive standard self-care education (e.g., maintaining cleanliness, avoiding strenuous exercise and pressure, and using sun protection) at the start of chemotherapy. Clinical pharmacists monitor the volume of study drugs used by checking the remaining amount and educate the patients to improve their adherence, if necessary.

### Prohibited therapy and drugs

The following treatments or concomitant use of drugs are prohibited: (i) cancer treatment other than the capecitabine-based chemotherapy (localized radiation therapy excluding the palm or sole is allowed), (ii) continuous use of other topical corticosteroids or NSAIDs on the palms or soles, (iii) continuous use of NSAIDs, (iv) continuous use of pyridoxine, and (v) use of multi-kinase inhibitors.

### Discontinuation of interventions

Interventions are discontinued if any of the following events occurs: (i) discontinuation of capecitabine for any reason, (ii) withdrawal of consent, (iii) serious adverse events induced by the study drugs, and (iv) use of prohibited therapies or drugs. Optimal medical care without the study drugs is guaranteed to participants who discontinue or deviate from the intervention protocols.

### Evaluation

Patients complete a self-report check sheet daily to document symptoms of HFS and adherence to the study drug. Patient’s symptoms and laboratory tests results are reviewed at every visit, and the severity of HFS is assessed by the clinical pharmacist and attending physician by referring to the self-reported adverse events (Tables 2 and 3). Evaluators will be undergo regular training to ensure data quality.

**Table 2 Tab2:** Assessment schedule

			Chemotherapy period (weeks)			
		Pretreatment	3	6	9	12
Performance status		✓	✓	✓	✓	✓
Blood test		✓	✓	✓	✓	✓
Hand-foot syndrome			✓	✓	✓	✓
Peripheral sensory neuropathy			✓	✓	✓	✓
Nausea			✓	✓	✓	✓
Vomiting			✓	✓	✓	✓
Appetite loss			✓	✓	✓	✓
Diarrhea			✓	✓	✓	✓
Oral mucositis			✓	✓	✓	✓
Pigmentation			✓	✓	✓	✓
Abnormality of liver function			✓	✓	✓	✓
Abnormality of renal function			✓	✓	✓	✓
Neutropenia			✓	✓	✓	✓
Self-report (adverse events)			✓	✓	✓	✓
Self-report (self-adherence)			✓	✓	✓	✓
Dose of chemotherapy			✓	✓	✓	✓
Postponement of chemotherapy			✓	✓	✓	✓
Discontinuation of chemotherapy			✓	✓	✓	✓

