### Endpoints

The primary endpoint is the incidence of grade ≥ 2 HFS within 3 months. Secondary endpoints include time to onset of grade ≥ 2 HFS, time to onset of grade ≥ 1 HFS within 3 months, incidences of dose reduction, schedule delay, discontinuation due to capecitabine-induced HFS, an incidence of grade ≥ 2 peripheral sensory neuropathy (subgroup analysis will be performed in patients treated with oxaliplatin), and incidences of any grade capecitabine-related adverse events (nausea, vomiting, appetite loss, diarrhea, oral mucositis, pigmentation, abnormality of liver and renal functions, and neutropenia).

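### Table 2 schedules no pretreatment grade for peripheral sensory neuropathy, so carried-in neuropathy cannot be separated from new neuropathy in a secondary incidence endpoint

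*Protocol article*

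**What the plan says.** Table 2 in the Evaluation section has a pretreatment column and columns for weeks 3, 6, 9 and 12. The pretreatment column is ticked for two rows only, performance status and blood test. The rows "Peripheral sensory neuropathy" and "Hand-foot syndrome" are ticked at the four on-treatment visits and blank at pretreatment.

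The Endpoints section lists among the secondary endpoints "an incidence of grade ≥ 2 peripheral sensory neuropathy (subgroup analysis will be performed in patients treated with oxaliplatin"). It does not refer to a baseline grade. The Discussion gives the reason for the endpoint: avoiding grade 2 or higher HFS may ease some of the neuropathy symptoms caused by oxaliplatin.

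Two exclusions in the Participants section bear on status at entry. Exclusion (ii) reads, in part, "presence of other skin diseases, skin lesions due to chemotherapy on the palms or soles, or dermatitis that makes it difficult to evaluate the efficacy". Exclusion (viii) is "sensory palsy in the palms or soles". Previous neurotoxic treatment and existing neuropathy are not among the listed exclusions.

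**The concern.** The neuropathy endpoint is meant to capture something that happens during the trial. An incidence needs a starting state, and the printed schedule does not collect one. A patient who is grade 2 at week 3 may have reached that grade on treatment or may have arrived with it, and the scheduled data do not say which.

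An analysis plan can define incidence as new onset or worsening, but it cannot supply a grade that was not collected. Without that grade, prevalent cases cannot be set aside, and a chance imbalance between the arms cannot be adjusted for. The minimization factors (sex, planned capecitabine dose, institution) do not balance neuropathy directly.

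At stake is the sensitivity of one secondary comparison and its oxaliplatin subgroup. A lesser companion issue is time to onset of grade 1 or higher HFS: a mild skin change already present at entry could appear as an onset at the first assessment.

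**Working it through.** The plan gives no figure for neuropathy, so there is none to reproduce. The check is mainly a reading of the sections against each other, followed by an illustration.

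**Step 1, schedule against endpoint.** Table 2 first grades neuropathy at week 3. The cream starts on the evening of day 1 (Intervention). The Endpoints section counts grade 2 or higher. No scheduled assessment comes before exposure, so a change from baseline cannot be formed from scheduled data.

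**Step 2, does eligibility close the gap?** Exclusion (viii) uses the term sensory palsy, gives no grade and does not name neuropathy. It need not remove a patient with painful or tingling hands and preserved sensation. Exclusion (ii) mentions skin lesions due to chemotherapy, so pretreated entrants are foreseen. The gap is narrowed but not closed.

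**Step 3, direction of the effect.** Let *b* be the share of patients in each arm who enter at grade 2 or higher and are still graded so at some visit, whatever their arm. Let *p* be the true incidence among the rest. Then

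- observed rate: *P* = *b* + (1 − *b*)*p*
- observed difference: *P*₁ − *P*₂ = (1 − *b*)(*p*₁ − *p*₂)

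The difference shrinks by the factor 1 − *b* and keeps its sign. Because allocation is randomized and blinded, *b* has the same expectation in both arms.

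**Step 4, illustration for neuropathy.** Every input is an assumption: *n* = 100 oxaliplatin patients per arm, *p*₁ = 0.25, *p*₂ = 0.15, and *b* from 0 to 0.20. Power uses the normal approximation with *P̄* = (*P*₁ + *P*₂)/2:

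power = Φ{[(*P*₁ − *P*₂)√*n* − *z*√(2*P̄*(1 − *P̄*))] / √(*P*₁(1 − *P*₁) + *P*₂(1 − *P*₂))}

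For *b* = 0 at two-sided 5%: (0.10 × 10 − 1.96 × 0.5657)/0.5612 = −0.194, and Φ(−0.194) = 0.42.

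| *b* | *P*₁ vs *P*₂ | Difference (points) | Power, two-sided 5% | Power, one-sided 5% |
|---|---|---|---|---|
| 0 | 0.250 vs 0.150 | 10.0 | 42% | 55% |
| 0.05 | 0.2875 vs 0.1925 | 9.5 | 35% | 47% |
| 0.10 | 0.325 vs 0.235 | 9.0 | 29% | 41% |
| 0.20 | 0.400 vs 0.320 | 8.0 | 22% | 32% |

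One-sided 5% is the only significance level the article states, and it states it for the primary endpoint.

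**Step 5, the primary endpoint.** Here the document does give planning rates: 40% vs 25%, 160 per arm, one-sided 5% (Sample size calculation). The same formulas give 89.2% power at *b* = 0. At *b* = 0.02 the rates are 0.412 vs 0.265, the difference is 14.7 points and power is 87.4%. At *b* = 0.05 the difference is 14.25 points and power is 84.7%. Power drops just below 80% (79.8%) at *b* = 0.10, which would need one entrant in ten to have grade 2 or higher HFS despite exclusion (ii).

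**The case against.** **A blank cell does not prove that the value is never recorded.** The rows for neutropenia and for liver and renal abnormality are also blank at pretreatment, yet the blood test is ticked there, so those baseline values exist. The rows may be a schedule for grading events on treatment. The article condenses a fuller protocol and case report form, and charts may hold the grade. This stands: what can be said is that no pretreatment neuropathy grade is scheduled. Unlike the laboratory rows, however, neuropathy has no other ticked pretreatment row that would supply it.

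**A reader might infer that symptoms present at entry are counted as incident events.** The document has no counting rule for such symptoms, and an analysis plan may well contain one. The objection stands against that reading. It does not remove the point, because a rule for new onset or worsening needs a baseline grade to work on.

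**A reader might extend the point to the primary endpoint.** Exclusion (ii) cannot be applied without looking at the palms and soles before entry. On the natural reading it removes chemotherapy lesions there outright; on the looser reading it removes those that hamper evaluation. Carried-in grade 2 or higher HFS should be rare. This stands, and only minor changes relevant to grade 1 onset remain.

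**The illustration rests wholly on assumptions.** This also stands. The Discussion expects mostly colorectal patients on adjuvant treatment, and nothing in the documents supports a particular carried-in share. At *b* = 0 the assumed comparison already has low power. In addition, the printed exclusion list passes from (v) to (vii), so the full protocol may hold a criterion not seen here.

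**Conclusion.** The point holds as a modest improvement to a secondary endpoint. The printed schedule has no pretreatment neuropathy grade, the endpoint is an incidence of grade 2 or higher, and the only related exclusion is ungraded. On that schedule, carried-in and new neuropathy cannot be told apart.

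The consequence is dilution of the between-arm difference and lost precision. It is not a bias toward either arm, and it does not create a false positive. Its size cannot be determined from the documents; the tabulated 9.5 to 8.0 points against 10.0 show only how the dilution behaves under the stated assumptions. The primary endpoint is hardly touched, and the effect on HFS is mainly confined to time to onset of grade 1 or higher. The conclusion assumes that Table 2 is the complete schedule for these two assessments; if the full protocol already requires a pretreatment grade, only Table 2 and the endpoint wording need correcting.

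**What to change.** - Tick pretreatment for peripheral sensory neuropathy in Table 2.
- Define the endpoint as new onset of, or worsening from baseline to, grade 2 or higher, and apply the same definition in the oxaliplatin subgroup.
- Adjust the neuropathy comparison for the baseline grade, or stratify by it.
- Record the HFS grade of the palms and soles at entry as well. Exclusion (ii) already requires that they be looked at, and the record mainly protects time to onset of grade 1 or higher HFS.

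The cost is two extra fields at an existing visit. For patients already enrolled, the grade would have to be retrieved from the chart, and some values may be missing. The analysis should then state how patients without a baseline grade are handled.

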**Table 3 Tab3:**
[figure not shown]
Self-report of hand-foot syndrome and self-adherence check sheet

### Endpoints

The primary endpoint is the incidence of grade ≥ 2 HFS within 3 months. Secondary endpoints include time to onset of grade ≥ 2 HFS, time to onset of grade ≥ 1 HFS within 3 months, incidences of dose reduction, schedule delay, discontinuation due to capecitabine-induced HFS, an incidence of grade ≥ 2 peripheral sensory neuropathy (subgroup analysis will be performed in patients treated with oxaliplatin), and incidences of any grade capecitabine-related adverse events (nausea, vomiting, appetite loss, diarrhea, oral mucositis, pigmentation, abnormality of liver and renal functions, and neutropenia).

### Sample size calculation

Based on previous RCTs evaluating the preventive effect for HFS, the incidence of grade ≥ 2 HFS within 3 months in the control group without preventive measures was approximately 40% [19, 20, 36]. Accordingly, the incidence of grade ≥ 2 HFS in the placebo arm is assumed to be 40%. It is expected that diclofenac sodium 0.1% cream will suppress grade ≥ 2 HFS within 3 months by 15%, resulting in an anticipated incidence rate of 25%. With a power of 80% and one-sided α of 5%, the required sample size is 160 patients in each arm. Therefore, the target number of enrolled patients is 320. No interim analysis is planned. Sample size calculations will be performed using SAS Studio 3.8.

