## Discussion

This study investigates the preventive effect of topical diclofenac sodium 0.1% cream for capecitabine-induced HFS.

According to the Common Terminology Criteria for Adverse Events version 5.0, grade 2 HFS is defined as a painful skin change, including delamination, blistering, and bleeding, which significantly reduces patients’ QOL. It often leads to treatment interruption, dose reduction, or even discontinuation of capecitabine. Preventing grade ≥ 2 HFS is expected not only improve patients’ QOL but also maintain treatment intensity. As reducing the overall incidence of HFS is more clinically meaningful than merely delaying its onset, the incidence of grade ≥ 2 HFS within 3 months is set as the primary endpoint. The evaluation period is set at 3 months, because, in patients receiving eight courses (6 months) of capecitabine plus oxaliplatin as adjuvant chemotherapy after surgery of colorectal cancer, the incidence of HFS increased until the 4th course (at 3 months after the start of treatment) and then plateaued [37]. In addition, the median time of onset of grade ≥ 2 HFS induced by fluoropyrimidine anticancer drugs has been reported to be approximately 100 days [38, 39]. Therefore, evaluating the incidence of grade ≥ 2 HFS at 3 months is deemed appropriate as the primary endpoint. The majority of participants are expected to be patients with colorectal cancer, receiving capecitabine as adjuvant chemotherapy, which is typically recommended for at least 4 courses (3 months). In Japan, capecitabine plus oxaliplatin in combination with bevacizumab is the most commonly used palliative chemotherapy, with a reported median progression-free survival time of approximately 10 months [39]. The second major population will consist of patients with breast cancer. The median progression-free survival of capecitabine monotherapy in patients with advanced breast cancer has been reported as approximately 3.2 months [7]. Thus, it is expected that most participants will continue capecitabine for 3 months, facilitating the evaluation of the primary endpoint.

The expectation of a 15% reduction in the frequency of HFS is based on a study using celecoxib as the study drug, where the incidence of grade ≥ 2 HFS was reduced by approximately 20% compared with the placebo group [19, 20]. Based on these reports, we expect that a 15% reduction in incidence of HFS would provide a lower risk and equally effective preventive method compared to celecoxib.

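### The 40% placebo rate and the 20% celecoxib effect behind the sample size conflict with the protocol's own Table 1 and must be reconciled with the cited sources

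*Protocol article*

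**What the plan says.** The Sample size calculation section reports that, in earlier randomized trials, grade ≥ 2 HFS within 3 months "in the control group without preventive measures was approximately 40% [19, 20, 36". It concludes that "the incidence of grade ≥ 2 HFS in the placebo arm is assumed to be 40" (per cent). The active cream "will suppress grade ≥ 2 HFS within 3 months by 15%, resulting in an anticipated incidence rate of 25" (per cent). Then: "With a power of 80% and one-sided α of 5%, the required sample size is 160 patients in each arm", and "the target number of enrolled patients is 320".

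The Discussion justifies the 15-point effect by celecoxib trials in which grade ≥ 2 HFS "was reduced by approximately 20% compared with the placebo group [19, 20".

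Table 1 in the Introduction lists the same three references:

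| Reference | Blinded | Control n | Control, grade 2 or 3 | Control, grade ≥ 3 | Intervention n | Intervention, grade 2 or 3 |
|---|---|---|---|---|---|---|
| [19] celecoxib | No | 50 | 30% | 10% | 51 | 11.76% |
| [20] celecoxib | No | 71 | 29.6% | 8.5% | 68 | 14.7% |
| [36] teaching module | Yes | 134 | 32.8% | 6.8% | 135 | 33.3% |

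**The concern.** The placebo rate is one of the two inputs that fix the sample size for the only primary endpoint, and no interim analysis is planned at which it could be revisited. The section gives one basis for it, references 19, 20 and 36. As Table 1 reports them, none of those control arms reaches 33%. The second input, the effect size, rests on a celecoxib reduction that is also larger than Table 1 shows.

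If Table 1 is right, the planned 40% lies about 9 points above its stated source, and the 15-point target is close to the whole celecoxib effect rather than a cautious step down from 20. If the planning text is right, Table 1 misreports the trials on which the design is built. In either case a reader cannot tell which control rate the power statement should be judged against.

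**Working it through.** **1. Is the grade 2 or 3 column the endpoint?** The Introduction gives D-TORCH grade ≥ 2 HFS as 3.8% versus 15.0%. The D-TORCH row of Table 1 shows 3.8 and 15 under grade 2 or 3. At least in that row, the column is grade ≥ 2.

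**2. Control rate in the cited trials.** Size-weighted: (50 × 0.30 + 71 × 0.296 + 134 × 0.328) / (50 + 71 + 134) = 79.97 / 255 = 31.4%. Gap to the planning value: 40 − 31.4 = 8.6 points.

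**3. Celecoxib effect.** Reference 19: 30 − 11.76 = 18.2 points. Reference 20: 29.6 − 14.7 = 14.9 points. Pooled from the implied counts: (15 + 21)/121 − (6 + 10)/119 = 29.8% − 13.4% = 16.3 points. Table 1 lists both trials as not blinded, so calling the comparator a placebo group also needs checking.

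**4. Where 40% may come from.** Adding the grade 2 or 3 and grade ≥ 3 control columns:
- [19]: 30 + 10 = 40.0%
- [20]: 29.6 + 8.5 = 38.1%
- [36]: 32.8 + 6.8 = 39.6%

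If the first column already contains grade 3, this sum counts grade 3 twice. If it holds grade 2 only in these rows, the sum is right and the column label is wrong for them. The grade-2-only reading cannot hold for the D-TORCH control: 15 + 5.3 = 20.3%, above its any-grade rate of 18.1%. The China 2021 intervention arm points the other way: 4.8% for grade 2 or 3 but 6.0% for grade ≥ 3. The column may not be used consistently.

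**5. Power at 160 per arm, one-sided 5%.** Normal approximation with pooled variance under the null, p̄ = (p₁ + p₂)/2:

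power = Φ{[(p₁ − p₂) − 1.645 √(2p̄(1 − p̄)/n)] / √([p₁(1 − p₁) + p₂(1 − p₂)]/n)}

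The plan's own case, 40% versus 25%: (0.15 − 1.645 × 0.05237)/0.05169 = 1.236, power 89%. The stated 80% is not reproduced: this formula needs 120 per arm for 80%, or 133 with continuity correction. That is a separate matter, but it shows that 160 carries some reserve on the stated inputs.

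The planned relative risk is 25/40 = 0.625. At the Table 1 rates:

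| Control rate | Relative risk 0.625 held: active rate, power | 15 points held: active rate (relative risk), power |
|---|---|---|
| 40% (plan) | 25%, 89% | 25% (0.625), 89% |
| 32.8% [36] | 20.5%, 80% | 17.8% (0.54), 93% |
| 31.4% (weighted) | 19.6%, 78% | 16.4% (0.52), 94% |
| 30% [19] | 18.75%, 76% | 15% (0.50), 94% |
| 29.6% [20] | 18.5%, 75% | 14.6% (0.49), 95% |

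The weighted row uses 31.36%. With the relative effect held: (0.1176 − 1.645 × 0.04872)/0.04827 = 0.776, power 78%. With 15 points held: (0.15 − 1.645 × 0.04765)/0.04691 = 1.527, power 94%.

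**The case against.** **The trial is not underpowered.** A reader might infer that a control rate of 31% leaves the trial short of power, or that the stated power holds only at 40%. Neither follows. The plan expresses its effect as an absolute 15-point reduction, and with that held, power rises as the control rate falls. With the relative risk held instead, the weighted rate costs two points against the stated 80%. The relative risk of 0.52 then needed for 15 points is weaker than Table 1 shows for celecoxib (11.76/30 = 0.39 and 14.7/29.6 = 0.50) or for D-TORCH (3.8/15 = 0.25). This stands in full.

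**40% may be right.** The cited papers are not at hand, so the mismatch is established only between the planning text and Table 1. The grade-2-only reading gives about 40% for all three controls. It also moves the celecoxib differences to 26.3 points (40.0 − 13.72) and 20.5 points (38.1 − 17.6), the second of which fits the Discussion's figure. Separately, the Japanese controls in Table 1 are 60%, 34% and 50%, size-weighted (30 × 60 + 67 × 34 + 12 × 50)/109 = 42.9%. This also stands: replacing 40% by 31% outright would be premature. But the section does not cite the Japanese trials as its basis, and on the grade-2-only reading Table 1 needs correcting.

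**Two further inferences fail.** One might argue that D-TORCH is not unusual, because some other blinded controls lie near its 15%. The Introduction's sentence is about HFS in general: "the incidence of HFS in the placebo group of the D-TORCH study was substantially lower than that in other Asian studies (Table 1". For any grade, 18.1% against 52% to 83.3% in the other rows that report it bears this out. One might also argue that the placebo rate must fall still lower because "The hydrophilic cream, which is the base material of diclofenac sodium 0.1% cream, is selected as the placebo". No figure in the article sizes a preventive effect of the base, so that is conjecture.

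**Conclusion.** The point holds as an internal contradiction about both inputs to the sample size. The 40% attributed to references 19, 20 and 36 stands against 30%, 29.6% and 32.8% in Table 1, and the celecoxib effect of about 20% against 18.2 and 14.9 points. Of the two, the control rate is the clear conflict. The effect size taken alone might pass as loose rounding for reference 19, but not for reference 20 or for the pooled 16.3 points.

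The article does not decide whether the planning text or Table 1 is at fault. The consequence is bounded: if Table 1 is right, power at 160 per arm is 75% to 80% under a constant relative risk of 0.625 and 93% to 95% under a constant 15-point reduction. These figures assume 160 evaluable patients per arm, a one-sided 5% test and the normal approximation. They also take the Table 1 rates as 3-month rates, although the table states no time window.

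**What to change.** 1. Check references 19, 20 and 36, and reconcile the Sample size calculation, Table 1 and the Discussion with them.
2. If Table 1 is right, base the placebo rate on about 31%, or keep 40% and cite data that support it, for example the Japanese controls in Table 1 (34% to 60%). Correct the celecoxib effect to 15 to 18 points, and describe the comparator as the sources do.
3. If the planning text is right, correct the grade 2 or 3 entries or the column label in Table 1 for the affected rows.
4. In either case, state the power of 160 per arm at one-sided 5% over plausible control rates, for both a relative risk of 0.625 and a 15-point reduction. The table above can serve as a start.

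Cost: rewording in three places and one short power table. Enrolment stays at 320. The stated power may look less favourable if the lower control rate is correct and the relative effect is the one that carries over.
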